**Figure 2 F2:**
[figure not shown]
**Dose escalation design**. Three patients will be treated with the starting dose. If no DLT occurs, the next cohort will be treated with the next MAPC dose level. If one DLT occurs in a cohort, a second cohort of 3 patients will be treated with the same MAPC dose level. The study will be stopped if more than one DLT event is recorded after enrolling at most 6 patients.

Should one patient experience a DLT after 3 patients have been enrolled in any cohort, another 3 patients will be enrolled in the same dose group after consultation with the data safety monitoring board. If no further toxicity occurs, the next 3 patients will be enrolled at the next dose level. If a total of 2 or more patients experience a DLT, either after 3 or 6 patients have been enrolled, the study will be closed and the dose of the previous cohort will be considered the maximum-tolerated dose.

If no toxicities occur at all, the maximum dose administered in the study, i.e., 2 × 600 million MAPCs per patient, will be considered the maximum-tolerated dose and the study will be closed. Using the dose escalation scheme described above, between 3 and 24 patients will be enrolled in this study, with 12 patients being the optimal scenario. The study protocol was designed according to the declaration of Helsinki and approved by the local ethics committee.

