**Methods:**

Patients enrolled in this phase I, single-arm, single-center safety and feasibility study (n = 3-24) will receive 2 doses of third-party MAPCs after liver transplantation, on days 1 and 3, in addition to a calcineurin-inhibitor-free "bottom-up" immunosuppressive regimen with basiliximab, mycophenolic acid, and steroids. The study objective is to evaluate the safety and clinical feasibility of MAPC administration in this patient cohort. The primary endpoint of the study is safety, assessed by standardized dose-limiting toxicity events. One secondary endpoint is the time until first biopsy-proven acute rejection, in order to collect first evidence of efficacy. Dose escalation (150, 300, 450, and 600 million MAPCs) will be done according to a 3 + 3 classical escalation design (4 groups of 3-6 patients each).

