### Study Design

This is a phase I, single-arm, single-center safety and feasibility study based on a classical 3 + 3 dose escalation design. Safety of MAPC infusions is assessed by the occurrence of a dose-limiting toxicity (DLT) event (Figure 1) within 30 days after administration of the first MAPC dose. Because the focus in this study is on safety, a conservative dose escalation scheme rather than an accelerated titration design was chosen. The starting dose of 2 × 150 million MAPCs (MultiStem^®^) per patient has already been administered to patients for various indications, with no side effects observed so far. This dose corresponds to doses that have been shown to prolong graft survival in animal models. The maximum dose of 2 × 600 million MAPCs is still at least 50% lower than the maximum-tolerated dose in laboratory animals and similar to MSC doses already injected into patients [39].

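### The MTD label will usually rest on 0 DLTs in only 3 patients, which is a stronger conclusion than such data support

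*Protocol article*

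**What the plan says.** The Study Design section describes a "safety and feasibility study based on a classical 3 + 3 dose escalation design". The abstract gives four dose levels with 3 to 6 patients each. The rules in the Figure 2 legend and the text after it are:

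- 0 DLTs in 3 patients: "If no DLT occurs, the next cohort will be treated with the next MAPC dose level".
- 1 DLT in 3 patients: "another 3 patients will be enrolled in the same dose group after consultation with the data safety monitoring board". After that, "If no further toxicity occurs, the next 3 patients will be enrolled at the next dose level".
- 2 or more: "If a total of 2 or more patients experience a DLT, either after 3 or 6 patients have been enrolled", then "the study will be closed and the dose of the previous cohort will be considered the maximum-tolerated dose".
- No toxicity at any level: the top dose is named the MTD and the study closes.

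The same text gives a total of 3 to 24 patients and calls 12 the optimal case. Nothing in the Study Design or Dose-Limiting Toxicity sections brings a lower level up to 6 patients after a stop. The section on the data safety monitoring committee mentions starting the next cohort or expanding the current one, and not returning to a previous one.

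**The concern.** A dose is called the MTD on whatever data it has when the study closes. Because escalation follows 0/3, that is usually 3 patients without a DLT. After a stop, the label is also given just when the next level up has shown 2 or more patients with a DLT, which is when the evidence on the level below matters most.

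The primary endpoint is safety judged by DLTs, and the MTD is the dose conclusion that the plan draws from it. By the usual convention, a reader who sees an MTD from a classical 3 + 3 takes it to mean at most 1 DLT in 6 patients. That convention is general methodology and is not stated in the article. The label would therefore suggest more evidence than the trial has collected, unless the number treated and an interval stand beside it.

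**Working it through.** **Inputs from the article.** Four levels; 0/3 escalates; 1/3 expands to 6; 1/6 escalates; 2 or more patients with a DLT stops; no return to a lower level. The article gives no DLT rates, so every *p* below is an assumption.

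**1. The plan's own totals.** Stop in the first cohort of 3: 3 patients. All four levels expanded: 4 × 6 = 24. No DLT at all: 4 × 3 = 12. All three stated figures reproduce. The 12-patient case also shows that an MTD on 3 patients is intended, since the top dose then has exactly 3.

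**2. How often a cleared level has only 3 patients.** Let *p* be the DLT risk at a level.

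- Cleared on 0/3: (1−p)³.
- Cleared on 1/6: 3p(1−p)² × (1−p)³ = 3p(1−p)⁵.
- Share cleared on 3 patients: (1−p)³ / [(1−p)³ + 3p(1−p)⁵] = 1 / [1 + 3p(1−p)²].

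| p | 3p(1−p)² | share on 3 patients |
|---|---|---|
| 5% | 0.135 | 88% |
| 10% | 0.243 | 80% |
| 20% | 0.384 | 72% |
| 30% | 0.441 | 69% |
| 1/3 | 0.444 | 69% |
| 50% | 0.375 | 73% |

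The term 3p(1−p)² is largest at p = 1/3, where it equals 4/9. The share is then 9/13 = 69.2%, which is its minimum over all *p*. Given the per-level risks, a stop at the next level is independent of how the previous level was cleared, so the share also applies to the dose named after a stop. Enumerating all paths for assumed four-level profiles (for example 5/10/20/30%, 10/20/30/40%, 2/5/10/20%, and flat 10%, 20% and 30%), 69% to 83% of stops at level 2 or above name a dose given to only 3 patients.

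**3. What the data support (exact binomial limits).**

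| result | one-sided 95% upper limit | upper end of two-sided 95% interval |
|---|---|---|
| 0/3 | 1 − 0.05^(1/3) = 63% | 1 − 0.025^(1/3) = 71% |
| 0/6 | 39% | 46% |
| 1/6 | 58% | 64% |

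**4. What 6 patients at every cleared level would change.** The chance that a level clears now is (1−p)³ + 3p(1−p)⁵. If every cleared level needed at most 1/6, it would be P(at most 1 of 6).

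- p = 50%: 0.125 + 0.047 = 17.2% now; 7/64 = 10.9% with 6.
- p = 1/3: 43% now; 35% with 6.

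These are chances for one level taken alone, not chances that the dose ends up named the MTD.

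**The case against.** The strongest reply is that the rule is explicit, its totals are right, and it is a legitimate choice. Some 3 + 3 variants do not return to the lower dose, and the article says its design is based on the classical one. Closing after 2 patients with a DLT exposes no further patients. The word conservative in Study Design contrasts the scheme with accelerated titration and promises nothing about the MTD. All of this stands: the escalation and stopping rules are not shown to be wrong.

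Three stronger readings are tempting, and the document or the arithmetic does not support them.

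- *The declared MTD is carried into phase II/III.* The article does not say so. The abstract makes the next trial conditional on safety, the Discussion ties it to a confirmed lack of DLTs, and the Dose-Limiting Toxicity section describes DLTs as events that would halt development. MTD estimation is not among the listed objectives.
- *Six patients would settle the matter.* A 1/6 result has a one-sided limit of 58%, so it does not exclude a risk of one half either; only 0/6 would.
- *Requiring 6 would halve the chance of passing a dose with 50% risk.* Counting only the route through 0/3 gives 12.5% falling to 6.3%. That omits the route through 1/3; over all routes the fall is from 17.2% to 10.9%, about a third.

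Nor would filling the lower level always cost just 3 patients. At true risks of 20% to 40%, 3 further patients would show 2 or more DLTs with probability 3p²(1−p) + p³ = 10% to 35%, and the question would then move down one more level, although the total could not pass 4 × 6 = 24.

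None of this answers the narrower point, that 0/3 is given an unqualified MTD label.

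**Conclusion.** The point holds as an over-strong conclusion written into the decision rule. After a stop at level 2 or above, the named MTD rests on 0/3 in at least 69% of cases; in the no-toxicity branch the top dose always does. In both, a DLT risk of up to 63% (one-sided) or 71% (two-sided) is compatible with the data at the 95% level.

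The minimum of 69% needs no assumed DLT rate, only independent patients with a common risk within each level. Shares for particular rates and profiles do depend on assumed values. A previous level already expanded after 1/3 has 6 patients and is outside the point. A reader might infer that the protocol has made a mistake in its 3 + 3; it has not, and the point concerns only what is claimed from the result. It is worth acting on because the remedy is nearly free, not because the trial is unsound without it.

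**What to change.** In the Study Design text after Figure 2:

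1. Reconcile the MTD rule with the classical 3 + 3 named at the start of that section. Either say that this is a variant without return to the lower dose, or define what MTD means in this trial.
2. Do not give an unqualified MTD label to a dose treated in only 3 patients. Report it as the highest dose cleared in this study, with the number treated, the number of patients with a DLT and the exact interval, stating whether it is one- or two-sided (for 0/3: upper limit 63% or 71%).
3. Apply the same wording to the top dose in the 12-patient scenario, so that both MTD sentences follow one rule.

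This adds no patients and leaves escalation and stopping unchanged. The cost is a less favourable label and often no declared MTD, including in the scenario that the plan calls optimal. Whether to treat further patients at the lower dose after a stop is a separate matter that touches the stopping rule, and is left to the sponsor and the data safety monitoring committee.

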### Data safety monitoring committee

An independent data safety monitoring committee will be installed to monitor the study progress. The committee will include basic scientists and clinicians not otherwise involved in the trail. Members of this group will review the clinical and investigational data to ensure that participants are not exposed to undue risk. The data safety monitoring committee will review the data up to day 30 for each dosing cohort and will then give written recommendation on whether or not to continue the study. Members of the committee will also recommend on whether the next dosing cohort should start enrolment or whether the current cohort should be expanded. The data safety monitoring committee can recommend stoppage of the study for reasons of patient safety at any time. Whenever adverse events occur, the principal investigator and the study team will communicate those to the data safety monitoring committee in due time. If an adverse event is serious (SAE) or unexpected (SUSAR), the responsible authorities will be informed. About 10 SAEs might be expected in each liver transplant recipient transplanted with high MELD score during the first 30 days.

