The hypothesis is that MAPCs can prevent acute rejection episodes in the early post-transplant phase by interaction with recipient lymphocytes. We anticipate shifting the immune response towards a state of permanent graft acceptance that makes the escalation of pharmacological immunosuppression unnecessary. Moreover, we expect MAPCs to ameliorate ischemia/reperfusion damage to the graft, thereby avoiding late complications, such as hepatorenal syndrome and bile duct ischemia. The regenerative abilities of MAPCs could also reduce the occurrences of primary graft dysfunction and accelerate normalization of liver synthesis function especially in marginal liver grafts.

In summary, the expected clinical efficacy of MAPC infusions as an adjunct to established immunosuppressive pharmacotherapy is substantial and the potential benefits outweigh the expected risks. MAPCs have already been administered in about 50 patients with no specific severe side effects reported [55]. MSCs, which can be considered similar to MAPCs in terms of their safety profile, have been administered in over 200 patients with no reported malignancies or severe side effects [56]. If the lack of dose-limiting toxicities can be confirmed in the present study, we intend to conduct a second, larger study to assess the immunomodulatory and regenerative efficacy of MAPC infusion in liver transplantation. A positive outcome from MAPC therapy trials in terms of reducing the need for pharmacological immunosuppression would represent a major advancement for liver transplant recipients.

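### With no DLT at any level the plan calls 2 × 600 million the maximum-tolerated dose, although the MTD would not have been reached, and two other end states get no MTD conclusion

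*Protocol article*

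**What the plan says.** The Study Design section describes a trial "based on a classical 3 + 3 dose escalation design". The abstract gives the doses, "Dose escalation (150, 300, 450, and 600 million MAPCs) will be done according to a 3 + 3 classical escalation design", and the size, "4 groups of 3-6 patients each". Each dose is given twice.

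The rules, from the Study Design text and the Figure 2 caption, are:

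- **0 of 3 with a DLT:** "If no DLT occurs, the next cohort will be treated with the next MAPC dose level".
- **1 of 3:** three more patients are treated at the same level. If none of them has a DLT (1/6), the trial moves to the next level.
- **2 or more, among 3 or 6 patients:** the study closes, and the dose of the cohort before is taken as the MTD.
- **Nothing observed:** "If no toxicities occur at all, the maximum dose administered in the study", identified as "2 × 600 million MAPCs per patient, will be considered the maximum-tolerated dose and the study will be closed".

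Enrolment is put at 3 to 24 patients, with 12 as the best case.

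**The concern.** There are two faults.

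First, an MTD is located by finding a dose that is not tolerated and stepping back from it. In the no-DLT case the trial finds no such dose, so the label states something the data cannot show. This is also the case the plan hopes for: its best-case 12 patients are 0/3 at all four levels.

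Second, only two sentences assign an MTD, and they do not cover all the ways the trial can end. If the first dose is stopped, there is no earlier cohort to name. If the top level is cleared after a single DLT at any level, the stopping sentence does not apply and the no-toxicity sentence is not satisfied. With 1/6 at the top level, the text points to a next level that does not exist.

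At stake is what the report may conclude about dose, and whether that conclusion is fixed before the data are seen.

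**Working it through.** **Inputs.** Four levels, 3 or 6 patients per level, and the escalation, expansion and stopping rules are all from the Study Design section and the abstract. The per-patient DLT risk *p* is not given. It is assumed constant over doses and varied from 1% to 30%.

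**1. The plan's own figures.** A level can end as 0/3 (cleared), 1/6 (cleared), ≥2/3 (stop) or ≥2/6 (stop).

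- Minimum: ≥2/3 at level 1 gives 3 patients.
- Maximum: six patients at each level gives 4 × 6 = 24.
- No DLT: 4 × 3 = 12.

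All three stated numbers are reproduced. The minimum of 3 arises only through a stop in the first cohort, so the plan counts that outcome in its sample size but gives it no MTD conclusion.

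**2. End states against the two MTD sentences.** Completing all levels can happen in 2⁴ = 16 ways. Stopping at levels 1 to 4 can happen in 2 + 4 + 8 + 16 = 30 ways. The total is 46.

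| End state | Paths | MTD according to the text |
|---|---|---|
| Stop at levels 2 to 4 | 28 | Dose of the previous cohort |
| All four levels 0/3 | 1 | 2 × 600 million (the disputed label) |
| Stop at level 1 | 2 | None stated |
| All levels cleared, at least one at 1/6 | 15 | None stated |

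Of the 15, 8 have 1/6 at the top level; 7 have 0/3 at the top and 1/6 somewhere below. In all, 17 of the 46 paths have no stated MTD.

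**3. What zero DLTs can show.** With 0 events in *n* patients the exact upper limit is 1 − 0.05^(1/n) one-sided and 1 − 0.025^(1/n) two-sided.

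- Top dose, n = 3: 1 − 0.05^(1/3) = 63.2%; 1 − 0.025^(1/3) = 70.8%.
- All doses pooled, n = 12: 1 − 0.05^(1/12) = 22.1%; 1 − 0.025^(1/12) = 26.5%.

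A top dose with a true DLT rate of 30% shows 0/3 with probability 0.7³ = 34.3%; at 50% it is 0.5³ = 12.5%.

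**4. How often the uncovered states occur.** P(0/3) = (1−p)³ and P(1/6) = 3p(1−p)⁵; their sum *c* is the chance of clearing a level. Then:

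- stop at level 1: 1 − c
- complete with no DLT: (1−p)¹²
- complete with at least one DLT: c⁴ − (1−p)¹²

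For p = 10%: c = 0.729 + 0.177 = 0.906. The stop at level 1 is 9.4%, and completion with a DLT is 0.674 − 0.282 = 39.2%. Together they make 48.6%.

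| Assumed p | No DLT | Complete, ≥1 DLT | Stop at level 1 | Stop at levels 2–4 | No MTD stated |
|---|---|---|---|---|---|
| 1% | 88.6% | 10.9% | 0.1% | 0.4% | 11.0% |
| 2% | 78.5% | 19.7% | 0.5% | 1.4% | 20.2% |
| 5% | 54.0% | 35.8% | 2.7% | 7.6% | 38.4% |
| 10% | 28.2% | 39.2% | 9.4% | 23.2% | 48.6% |
| 20% | 6.9% | 18.3% | 29.1% | 45.6% | 47.5% |
| 30% | 1.4% | 4.6% | 50.6% | 43.5% | 55.2% |

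The last column is summed before rounding.

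**The case against.** The defence has real weight on consequence. The wording is a convention (the dose is to be *considered* the MTD), and the same sentence identifies it as the highest dose given. The Study Design section also discloses that this dose lies at least 50% below the animal MTD. The MTD is neither an objective nor an endpoint: the primary endpoint is DLT occurrence, which is observed in every end state. Wide limits after 0/3 belong to any 3 + 3 cohort. Most of the uncovered probability at low risk is completion with a DLT (35.8 of 38.4 points at 5%), where every level has passed the stated rule and a reader could guess the intended conclusion. The drawing in Figure 2 is not available and might label these states, although its caption does not. All this limits the severity. It does not make the label correct or the rule complete.

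A reader might go further in three ways that the article does not support.

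- **That the no-toxicity condition can never be met**, because "About 10 SAEs might be expected in each liver transplant recipient". Those are background events in high-MELD recipients during the first 30 days. The Study Design text uses toxicity to mean DLT, as in its rule for the second group of three patients, so the condition can be met.
- **That the Discussion contradicts the escalation rule** when it says "If the lack of dose-limiting toxicities can be confirmed in the present study". That is a statement of intent about a later study. It is not a go criterion and does not say what follows a single DLT.
- **That the trial would yield no result, or that a mislabelled MTD becomes the phase II/III dose.** Only the MTD label is missing in the uncovered states, and nowhere does the article say that the MTD sets the dose of the next trial.

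**Conclusion.** The point holds as a should-fix. In the plan's own best case the stated conclusion is wrong: 0/3 at every level shows that the MTD was not reached. The data at the top dose would then be compatible with a DLT rate of up to 63% (one-sided) or 71% (two-sided). This part needs no assumption about the DLT rate.

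The two gaps follow from the text alone. How often they would matter depends on an assumed constant DLT risk: 20%, 38% and 49% of trials at 2%, 5% and 10%. The DLT definition is described as a high barrier, so low rates may be the more relevant ones; even 1% leaves 11%.

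**What to change.** Replace the no-toxicity sentence with one that covers every completed trial, for example: *If all four levels are cleared under the stated rule (0/3 or 1/6 patients with a DLT), the MTD was not reached and 2 × 600 million is the highest dose tested.* Add: *If the study stops at the first level, the MTD is not established and is reported as below the starting dose.* Write DLTs in place of toxicities, so that the condition uses the defined term. Report the DLT proportion with an exact 95% interval per level and pooled.

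The cost is a few sentences and one small table. The escalation and stopping rules, the sample size of 3 to 24 and the conduct of the trial stay as they are. The only downside is a slightly less favourable stated conclusion in the best case.

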### Trial Population

Patients of both genders and any ethnic origin aged 18 years or older will be screened at the Department of Surgery, University Hospital Regensburg, and enrolled into the study if they meet the eligibility criteria given in Figure 3. All suitable patients will be informed about the study during a regular outpatient visit and asked for their willingness to participate. Specific study related risks such as the possible transmission of xenopathogens following cell culture with bovine serum will be explained. At our institution annually 70-80 patients are placed on the European Liver Transplant Waiting List. Therefore, to enroll 3-24 patients for the study, a recruitment period of 12 months is anticipated.

**Figure 3 F3:**
[figure not shown]
Inclusion and exclusion criteria of the study.

### Interventions

#### Pre- and Intraoperative Data

Patients enrolled in this study will not need to undergo additional screening visits or clinical investigations in addition to standard pre-transplant work-up. Standard-of-care examinations for patients on the Liver Transplant Waiting List will be performed, including baseline clinical data (demographics, medical history, current medication), physical examination, laboratory examinations, infection screening, urinalysis, electrocardiogram, echocardiography, chest X-ray, triple-phase abdominal computed tomography with intravenous and oral contrast, pulmonary function tests, and arterial blood gas analysis. Intraoperative data (warm and cold ischemia time, blood loss, requirement for blood products, incision-to-suture time) and donor data (age, serum sodium and gamma-GT levels, body mass index, infection status, cause of death, time on intensive care unit) will also be documented.

#### Treatment Regimen

Immunosuppression will be tailored to the individual needs of each patient in a "bottom-up" approach. The immunosuppressive protocol used in this study is already being applied at our center in patients with an expected low risk for rejection (MELD score > 25, particularly with preoperative renal dysfunction). Prior to liver reperfusion, 500 mg prednisolone will be administered intravenously. The cell product stored in liquid nitrogen at our hospital blood bank will be thawed by a qualified person and prepared for application. After liver reperfusion, the transplant surgeon will infuse the first MAPC dose from the freshly thawed cryobag directly into the portal vein using a small catheter.

On days 1 and 5, 20 mg of basiliximab will be administered for induction therapy as one key element of the institution's immunosuppressive regimen. There is a growing body of evidence indicating that basiliximab can impair the development of transplant tolerance by preventing the development of regulatory T cells [40-43]. Since we anticipate that omitting basiliximab will not influence MAPC toxicity, we have chosen to retain basiliximab yet to focus solely on safety in this study. More preclinical data is then needed to establish a causal relationship between basiliximab and putative MAPC effects. If it turns out that MAPCs depend on intact interleukin-2 signaling, the application of basiliximab in a subsequent efficacy study has to be critically discussed.

Maintenance immunosuppression will be conducted with 2 g/d mycophenolic acid (MPA) given as a split dose twice daily. Steroids at a dose of 1 mg/kg body weight will be commenced on day 1 and tapered successively. On day 3, the second MAPC dose will be administered intravenously in the intensive care unit. All patients will be monitored in a fully equipped tertiary intensive care unit before and for at least 48 hours after the cell infusion (see Figure 4).

